### Demographic information

Participants will complete a baseline survey with relevant repeated questions at weeks 13 and 26. The surveys will include questions on age, education, occupation, income, health history, and smoking history.

### Self-reported health and behaviour

*Well-being* will be measured with the SF36 (physical and mental summary scores and eight subscales (including vitality) [16]. *Motivation* will be assessed with the Behavioural Regulation in Exercise Questionnaire (BREQ-2) [17].

### Data analysis

The aim of this study is to obtain data on the effects of HIIT training on smoking cessation and intermediate outcomes, such as cigarette cravings and withdrawal symptoms. Using effect size estimates based on results of a previous study using vigorous PA for smoking cessation in women (i.e. OR = 2.09, [18]), adopting a two tailed alpha level of 0.05 and power 0.80, a sample size of 100 will be required. Based on funding and time constraints, the study aims to recruit 50 participants per group. Descriptive statistics will be used to summarize the characteristics of participants in each group, and to describe those who successfully quit. Yates’ corrected Chi-squared test will be used to analyse the difference in the proportions who quit in each group, and changes in categorical (e.g. smoking abstinence) and continuous (e.g. number of cigarettes smoked) variables will be assessed using generalised linear modeling.

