### Aims

The aims of this project are to: (1) compare the effects of two exercise interventions (HIIT and a ’10,000 steps’ pedometer based intervention) combined with usual care smoking cessation support, on cessation rates in female smokers who wish to quit; (2) assess the effects of HIIT and 10,000 steps interventions on weight change and (3) assess whether improvements in fitness, vitality and intrinsic motivation are mediators of the relationship between activity and smoking cessation.

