### Intervention

*Usual care cessation support:* Participants in both groups will receive usual care smoking cessation support, based on the Smoking Cessation Guidelines for Australian General Practice [11] This includes a quit pack (available from Quitline), which covers planning and preparing to quit, strategies for quit success, and coping with cravings. Participants will also be directed to other resources, including the ‘My QuitBuddy’ mobile app, and the web-based QuitCoach. These resources provide personalized quit plans, monitor progress and money saved, and motivation and support from others using the app. Participants will also be directed to call Quitline should they wish to speak to a counsellor about their quit attempt. Quitline is a confidential service with a professional advisor available for counseling and advice on quitting smoking.

*10,000 steps pedometer group:* participants assigned to this group will receive a resource pack and pedometer, and will be asked to increase their daily steps to 10,000. The resource pack contains a log-book to record steps/day, number of cigarettes smoked, and hints and tips for increasing step counts. The log-book is based on resources used by the Queensland 10,000 steps project (www.10000steps.org.au) Trained research staff will phone these participants once a week to check and record pedometer use and discuss barriers and strategies for successfully increasing PA.

*HIIT group:* participants assigned to this group will complete two gym-based supervised sessions (supervised by trained research staff) and one home-based HIIT session each week. The HIIT protocol will be completed by fast walking or running on a treadmill with the deck inclined to reach the desired intensity, or on a cycle ergometer if individuals are unable or do not wish to use the treadmill. The 35 min protocol consists of: warm-up at 65 % of heart rate maximum (HRmax) (5 min); 4 **×** 4 min intervals at 85–95 % HRmax (with the target zone reached by at least two minutes), interspersed with 3 min recovery at 65 % HRmax; and cool down (5 min), with a total exercise time of 35 min (see Fig. 2). Attendance at supervised sessions and adherence to home-based sessions (including compliance with target heart rate) will be monitored and recorded by research staff.

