## Discussion

Physical inactivity and tobacco smoking are important contributors to the overall burden of disease in Australia, and are significant risk factors for almost all Australia’s major non-communicable physical and mental health problems.

This study is innovative, as it will build on suggestions from previous studies that intensity of exercise may be a critical factor in determining the efficacy of PA interventions for smoking cessation. Our study addresses this issue by comparing the effect of two PA interventions of varying intensity on smoking cessation outcomes.

In examining the notion that HIIT (combined with a quit program) will result in higher quit rates than a more moderate PA intervention, we will also examine novel mediators (fitness, vitality and intrinsic motivation) which will improve understanding of the relationships between HIIT and smoking cessation.

Further, we will assess the effect of exercise intensity on other indicators of smoking, such as withdrawal symptoms, cigarette cravings and weight gain, as these factors are important barriers to smoking cessation. This project will address the weaknesses of previous studies (e.g. poor assessment of intensity, adherence or compliance to exercise) and is novel in design and conceptualisation.

HIIT has potential to impact on individual cardiovascular health and to be a very cost effective intervention, compared with other cardiovascular treatments (e.g. statins), as it may address two major contributors to cardiovascular disease (smoking and physical inactivity) in one intervention. The research will inform efforts to develop novel, innovative, and time efficient strategies for promoting cardiovascular health in women.

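### The sample size rests on an OR of 2.09 that is not shown to apply to HIIT versus an active steps programme, and 50 per group does not give the stated 80% power even at that OR

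*Protocol article*

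**What the plan says.** The sample-size statement is in the Data analysis section of the protocol article. The planning effect comes from elsewhere: "Using effect size estimates based on results of a previous study using vigorous PA for smoking cessation in women (i.e. OR = 2.09, [18". It is combined with the error rates, "adopting a two tailed alpha level of 0.05 and power 0.80", and the result is that "a sample size of 100 will be required". The next sentence cites limits of money and time and says that "the study aims to recruit 50 participants per group". Quit proportions are to be compared with a Yates-corrected chi-squared test. No control quit rate is given for the calculation.

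The comparison being sized is set out under Aims, which is to "compare the effects of two exercise interventions (HIIT and a ’10,000 steps’ pedometer based intervention) combined with usual care smoking cessation support". The Intervention section describes the steps arm: a resource pack, a pedometer, a log-book, a daily step goal and staff contact, in that "Trained research staff will phone these participants once a week to check and record pedometer use and discuss barriers and strategies for successfully increasing PA". The Discussion presents the contrast as one of intensity: "Our study addresses this issue by comparing the effect of two PA interventions of varying intensity on smoking cessation outcomes".

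**The concern.** A sample size is only as good as the match between its planning effect and the contrast the trial randomises. The article describes the source of the OR only as "a previous study using vigorous PA for smoking cessation in women". That identifies one arm of the earlier study and says nothing about the other. In this trial the other arm is a structured exercise programme with weekly contact. The effect separating the arms is what HIIT adds over steps, and the article gives no reason to expect an OR of 2.09 for that.

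The stated power frames the whole study. A reader who sees 80% power and a non-significant difference may take the result as informative about exercise intensity, which is the question the Discussion poses. If the design has far less power, including at the planning OR, such a result would say little.

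**Working it through.** **Inputs from the article.** OR 2.09; two-sided alpha 0.05 (z = 1.960); power 0.80 (z = 0.842); 100 women in total, 50 per group; Yates-corrected chi-squared test.

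**Inputs not in the article.** The control quit rate p1 is not stated, so every value from 0.5% to 99.5% was scanned. The only quit rate in the article is the 5% in the Background for unaided quitters at 6 months. The rates of 20% and 41% below are assumptions; 41% is about the rate most favourable to the plan. No dropout allowance is stated and none was applied.

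**Step 1: reproduce the plan's figure.** The HIIT quit rate is p2 = OR·p1/(1 − p1 + OR·p1). With pm the mean of p1 and p2, the number per group is

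n = [1.960·√(2pm(1−pm)) + 0.842·√(p1(1−p1)+p2(1−p2))]² / (p2−p1)².

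At p1 = 0.41: p2 = 0.8569/1.4469 = 0.592, pm = 0.501, difference 0.182. The numerator is (1.960×0.7071 + 0.842×0.6953)² = 1.971² = 3.885. Dividing by 0.1822² = 0.0332 gives 117 per group, 234 in total. This is the minimum over all control rates. At 20%, 10% and 5% the totals are 302, 494 and 898. Other routes do not reach 100 either: the minimum is 256 with a continuity correction, 240 on the log-OR scale and 186 with a one-sided test. If 100 meant per group, power would still be at most 73%. A total near 100 (98) appears only if 2.09 is treated as a risk ratio with a 25% control rate, and the article says neither.

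**Step 2: power at 50 per group and OR 2.09.** Power = Φ{[(p2−p1)·√50 − 1.960·√(2pm(1−pm))] / √(p1(1−p1)+p2(1−p2))}.

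- p1 = 0.41: (0.1822×7.071 − 1.386)/0.6953 = −0.14, so power is 44%, the maximum over all control rates.
- p1 = 0.20 (p2 = 0.5225/1.5225 = 0.343): (0.1432×7.071 − 1.233)/0.6208 = −0.355, so power is 36%.
- p1 = 0.10 and 0.05: 24% and 15%.

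**Step 3: the planned test.** Exact power of the Yates test sums the binomial probabilities of every pair of quit counts (0 to 50 in each arm) for which the corrected statistic exceeds 3.841. At OR 2.09 it is 6%, 16%, 29% and 39% for control rates of 5%, 10%, 20% and 41%.

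**Step 4: what an active comparator could do.** Suppose the cited OR is against no exercise, HIIT matches it, and steps have an OR of s against no exercise. The HIIT-versus-steps OR is then 2.09/s. The article states none of these premises; they only show sensitivity.

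| s (assumed) | HIIT vs steps OR | Exact Yates power, 20% steps-arm quit rate | Exact Yates power, 41% |
|---|---|---|---|
| 1.0 | 2.09 | 29% | 39% |
| 1.1 | 1.90 | 22% | 30% |
| 1.2 | 1.74 | 16% | 23% |
| 1.5 | 1.39 | 7% | 10% |

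**The case against.** The strongest reply is that the article never says what the earlier study compared vigorous activity with. A reader might infer that the 80% belongs to a different comparison, vigorous exercise against none. The document does not establish that: the comparator could have been lighter activity or a contact control. The Discussion does not settle it, because its remarks on intensity and innovation say nothing about the cited study's control arm. This stands, so the mismatch is a possibility the plan leaves open, not a demonstrated fact.

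A reader might also infer that using 2.09 assumes steps do nothing for quitting. That does not follow either. The same OR would hold if steps help and HIIT exceeds the cited programme by the same factor. Nor would little effect of steps contradict the Background, which calls the evidence on quitting mixed and names low intensity as a possible reason for earlier null trials.

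It would also be wrong to start from 80% and report how far an effective steps arm pulls it down, since the design does not have 80% at OR 2.09.

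Finally, how a null result will be worded and which estimate leads the report are reporting choices that may be left to a full protocol or analysis plan. The article also openly says that resources set the recruitment target. Both points are fair. Neither removes the power claim or ties the OR to this comparison.

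**Conclusion.** The point holds in two parts. First, the plan carries an OR of 2.09 from an earlier vigorous-activity study into a comparison of HIIT with another active programme, without naming the earlier comparator or defending the transfer. Whether the true contrast is smaller depends on that comparator, on whether steps aid quitting, and on how HIIT compares with the cited programme; the document gives none of these.

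Second, and needing none of those assumptions, 100 women do not give 80% power at OR 2.09. Two-sided power is at most about 44% at any control quit rate, or about 39% with the planned test, and at least 234 women would be needed. Correcting the arithmetic alone would still leave the planning effect untied to the comparison. If the relevant OR were 1.74, Yates power would be about 16% to 23% at assumed steps-arm quit rates of 20% to 41%. The statement is wrong as written and should be corrected.

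**What to change.** In the sample-size paragraph of the Data analysis section:

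1. Name the comparator behind OR 2.09, and say whether the OR is carried over to HIIT versus steps as an assumption.
2. Drop the claim that 100 women give 80% power.
3. Keep 50 per group and present it as the number that funding and time allow.
4. State the power of the Yates test, or the expected 95% confidence interval for the OR, for HIIT versus steps over a stated range of ORs (for example 1.4 to 2.09) and control quit rates.

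As an example of item 4, at OR 2.09 and a 20% steps-arm quit rate the standard error of the log OR is √[1/(50×0.2×0.8) + 1/(50×0.343×0.657)] = 0.462. The expected interval is 2.09 divided and multiplied by exp(1.96×0.462) = 2.47, or about 0.84 to 5.2.

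The change is to wording only and needs no extra participants, visits or measures. The downside is a less favourable stated power.

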## Background

Tobacco smoking is a major cause of cardiovascular disease, chronic obstructive pulmonary disease and many cancers. In women, research has shown that between the ages of 18 to 55 years, the largest population risk for heart disease is attributable to smoking (particularly in young women) and physical inactivity [1]. Despite steady declines in smoking prevalence over the past thirty years, in 2011–12, 16 % (1.4 million) of Australian women aged 18 years and over smoked daily. The 2009 National Preventative Health Strategy calls for a target of 10 % or less for smoking prevalence by 2020. This target will not be reached unless rates of cessation substantially increase [2]. More than half of all smokers want to quit [3], but many struggle to achieve abstinence, and relapse is common, with only 5 % of smokers who quit without any assistance still abstinent at 6 months [4]. As many smokers cite ‘wanting to get fit’ as a motivation for quitting [5], linking strategies that will simultaneously promote improvement in fitness and assist quitting has the potential to change both behaviours simultaneously [6].

There is evidence for a positive effect of exercise when quitting smoking [7], with physical activity (PA) reducing cigarette cravings and withdrawal symptoms [8]. However, the evidence for the efficacy of PA as an aid to quitting smoking is mixed. A recent systematic review of 15 randomised controlled trials highlighted insufficient exercise intensity as a potential limitation of interventions tested in previous trials which did not improve smoking abstinence rates [7].

High Intensity Interval Training (HIIT) could overcome the potential limitation of insufficient intensity, by providing alternating short bursts of high intensity exercise with recovery periods of light exercise. HIIT provides rapid physiological adaptations, as indicated by improvements in maximal oxygen uptake (VO_2_max), anaerobic threshold and stroke volume [9, 10].

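### The stated requirement of 100 women for 80% power at an odds ratio of 2.09 is wrong: with 50 per group and the planned Yates test, power cannot exceed 39%

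*Protocol article*

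**What the plan says.** The Data analysis section of the protocol article bases its sample size on OR 2.09, taken from a previous trial of vigorous physical activity for smoking cessation in women. It states that, "adopting a two tailed alpha level of 0.05 and power 0.80, a sample size of 100 will be required". The next sentence refers to limits of funding and time and says that "the study aims to recruit 50 participants per group", which makes 100 in total. For the main comparison, Yates' "corrected Chi-squared test will be used to analyse the difference in the proportions who quit in each group".

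Neither the control quit rate nor the visit behind the calculation is given. The only abstinence rate in the document is in the Background: "only 5 % of smokers who quit without any assistance still abstinent at 6 months".

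**The concern.** For a comparison of two proportions, an OR alone does not fix the sample size; the control rate is also needed. The calculation therefore cannot be repeated exactly, but it can be tested by asking whether any control rate gives 100. An OR near 2 is a modest effect on a binary outcome, and 50 per group looks far too few to detect it.

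This matters because the first aim is to compare cessation rates, the abstract states the hypothesis that HIIT will help women quit, and a significance test is planned. If real power is well below one half, a non-significant result is the likely outcome even when OR 2.09 is true. A reader told that the trial had 80% power could take that result as evidence that HIIT does not help.

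**Working it through.** **Inputs from the Data analysis section:** OR 2.09; two-sided alpha 0.05 (z = 1.960); power 0.80 (z = 0.842); 50 per group; Yates-corrected chi-squared test. **Not given:** the control quit rate p0, so it was varied over nearly its whole range (1% to 97%).

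**Step 1. Quit rate in the HIIT group.** p1 = OR × o / (1 + OR × o), with o = p0/(1 − p0). For p0 = 0.10, o = 0.1111 and p1 = 0.2322/1.2322 = 0.188. For p0 = 0.41, p1 = 0.592.

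**Step 2. Try to reproduce 100.** With the pooled-variance formula,

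n per group = [1.960 √(2p̄(1 − p̄)) + 0.842 √(p0(1 − p0) + p1(1 − p1))]² / (p1 − p0)², where p̄ = (p0 + p1)/2.

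The smallest n is at about p0 = 0.41 (p̄ = 0.501, difference 0.1822):

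n = (1.960 × 0.7071 + 0.842 × 0.6953)² / 0.1822² = (1.386 + 0.585)² / 0.0332 = 117.

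With the continuity correction that matches the Yates test:

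n′ = (n/4) × [1 + √(1 + 4/(n × 0.1822))]² = 29.25 × (1 + 1.090)² = 128.

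The minimum total is therefore 234 (uncorrected) or 256 (corrected), which is 2.3 to 2.6 times the stated 100. Other formulas, each at its most favourable rate, give 115 (unpooled), 117 (arcsine) and 120 (log OR) per group. A one-sided test, which the plan does not use, would still need 93 per group.

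**Step 3. Actual power at 50 per group.** All 51 × 51 possible pairs of quit counts were enumerated. Each pair was weighted by its binomial probability and counted as significant if chi-squared exceeded 3.841.

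| Assumed control rate | HIIT rate at OR 2.09 | Power, Yates | Power, uncorrected | n per group for 80%, uncorrected / corrected |
|---|---|---|---|---|
| 5% | 9.9% | 6.1% | 14.1% | 449 / 488 |
| 10% | 18.8% | 15.5% | 25.4% | 247 / 269 |
| 20% | 34.3% | 29.1% | 36.6% | 151 / 164 |
| 30% | 47.2% | 35.4% | 43.3% | 124 / 136 |
| 41% (maximum) | 59.2% | 39.1% | 47.1% | 117 / 128 |

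**Step 4. Read 100 as 100 per group.** Exact power then peaks at 70.5% (Yates) or 75.2% (uncorrected), again at 41%. It still misses 80% at every control rate.

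**Step 5. What 50 per group can detect.** With 80% exact power and Yates, the detectable OR is 4.7 at a 10% control rate (34% against 10%) and 3.7 at 20% (48% against 20%).

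**Step 6. Precision.** If OR 2.09 is observed with a 10% control rate, SE(log OR) = √[1/(50 × 0.10 × 0.90) + 1/(50 × 0.188 × 0.812)] = √(1/4.5 + 1/7.63) = 0.594. The 95% CI is 2.09 × exp(±1.96 × 0.594), about 0.65 to 6.7.

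**Where 100 may have come from.** One variant comes close: treating 2.09 as a risk ratio with a control rate of 25% gives 49 per group (98 in total) uncorrected. The text says OR and names no such rate, and exact Yates power at 50 per group would still be 75%. Converting the OR to a standardised mean difference (0.41) gives 96 per group, which matches neither the total nor the planned test.

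**The case against.** The core arithmetic is hard to dispute, but several points can fairly be made for the plan.

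- **The lower power figures are conditional.** The 6% rests on a 5% control rate, which the Background gives for people quitting unaided. The comparison group here is motivated and receives a quit pack, app, Quitline referral, pedometer and weekly calls, so its rate may be higher. This stands. The 39% ceiling needs no assumption about the control rate; the other figures do.
- **The text already admits a practical limit.** It cites funding and time and describes the aim as obtaining data. That is true, but the claimed requirement sits beside it. Since 2 × 50 = 100, the reader concludes that the requirement is met. The article does not call the trial a pilot.
- **A condensed article may leave the control rate, the visit and any dropout allowance to the full protocol.** This is fair, and the finding does not depend on those gaps. Since no control rate gives 100, the error lies in what is stated. Under intention to treat, loss to follow-up need not shrink the denominator for quitting either.
- **An estimation framing goes further than correcting a number.** It does change how the main comparison is presented. It follows from the corrected power, but it can be separated from the essential correction.
- **How readers would take a null result is a prediction.** That is so; the document does not say how such a result will be interpreted.

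**Conclusion.** The stated sample size is wrong as written. OR 2.09, two-sided alpha 0.05 and 80% power need at least 234 women uncorrected, or 256 for the planned test, at the most favourable control rate. The 100 planned give at most 39% power with Yates and 47% without, so even in the best case the planned test would miss a true OR of 2.09 at least 61% of the time. These limits hold over all control rates and rest only on the protocol's own inputs. The lower figures (6%, 16% and 29% at control rates of 5%, 10% and 20%) depend on those assumed rates. Reading 100 as per group does not rescue the claim and would mean recruiting half the stated need. This must be corrected, because it is the only statistical justification given for the trial's size.

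**What to change.** In Data analysis, delete the statement that 100 women are required for 80% power and replace it with text such as:

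*The sample size of 50 women per group was set by funding and time. Assuming a quit rate of [x]% in the 10,000 steps group at week [13 or 26], this gives [y]% power to detect an odds ratio of 2.09 with the Yates-corrected test at two-sided 0.05; an odds ratio of [z] could be detected with 80% power. The cessation comparison will be reported as an odds ratio and risk difference with 95% confidence intervals, and a non-significant result will not be interpreted as showing no effect.*

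For example, x = 10 gives y = 16 and z = 4.7; x = 20 gives y = 29 and z = 3.7. Whatever rate is chosen, y cannot exceed 39 with Yates (47 without). If the original calculation treated 2.09 as a risk ratio, this should be checked against the source and the effect measure corrected.

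The cost is wording, a less favourable power statement and a more modest framing of the cessation comparison. No extra participants or procedures are needed.

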### Data collection

Participants will be assessed on three occasions: at baseline, week 13 and week 26 (see Fig. 1). Cigarettes per day will be measured weekly. Withdrawal symptoms, cigarette cravings and feelings of stress, will be monitored during the intervention. See Table 2 for full list of measures, and measurement time-points. Exercise and fitness measures will be completed by research staff whom will be blinded to participant group allocation.

**Table 2 Tab2:** Timeline for data collection

	Measurement time-point					
Measures	Baseline	Week 2	Week 4	Week 8	Week 13	Week 26
Cigarettes per day (weekly)						
Smoking cessation					X	X
Withdrawal symptoms	X	X	X	X	X	X
Cigarette cravings	X	X	X	X	X	X
Cigarette dependence	X				X	X
Subjective stress	X		X	X	X	X
Saliva cotinine	X				X	X
Cardiorespiratory fitness	X				X	X
Lung function	X				X	X
Body composition	X				X	X
Physical activity	X				X	X
Well-being	X				X	X
Motivation	X				X	X
Demographic information	X				X	X

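### Yates' correction is valid but wasteful for the quit-rate test: at 50 per group its true size is 0.7% to 3.5%, which costs about 7 to 8 points of power at OR 2.09

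*Protocol article*

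**What the plan says.** The Data analysis section bases the sample size on an odds ratio of 2.09, "adopting a two tailed alpha level of 0.05 and power 0.80". It concludes that "a sample size of 100 will be required" and that "the study aims to recruit 50 participants per group". For the comparison of quit rates, it states that Yates' "corrected Chi-squared test will be used to analyse the difference in the proportions who quit in each group". The same sentence adds generalised linear modelling for changes in categorical variables, with abstinence as the example, and in continuous variables.

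The Data collection section says "Participants will be assessed on three occasions: at baseline, week 13 and week 26". Table 2 marks smoking cessation at week 13 and at week 26. The article does not say at which of these the Yates test is applied.

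No quit rate is given for the 10,000 steps arm. The only abstinence figure is in the Background: 5% "of smokers who quit without any assistance still abstinent at 6 months". That describes unassisted quitters, not this control arm.

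**The concern.** Yates' correction subtracts a fixed amount from the observed difference before the statistic is compared with the chi-squared cut-off. With 50 per group and quit rates that may be low, that amount is large relative to the differences that decide significance. The test then rejects a true null hypothesis far less often than the 5% the plan allows, and it also rejects a false one less often.

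What is at stake is efficiency. The section says that numbers are limited by funding and time, so power that can be recovered without recruiting anyone is worth having. The visit matters only alongside this. If the correction goes, its slack goes too, and two unranked tests of cessation would then carry a real multiplicity cost.

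**Working it through.** **Inputs.** From Data analysis: 50 per group (N = 100), two-sided alpha 0.05, odds ratio 2.09. Assumed: control quit rates of 5% to 50%, because the article gives none. The treated rate follows from p2 = 2.09·p1 / (1 − p1 + 2.09·p1).

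**The plan's own figure first.** The total of 100 is not reproduced. The usual formula per group is n = [1.96·√(2p̄(1−p̄)) + 0.8416·√(p1(1−p1) + p2(1−p2))]² / (p2−p1)². It is smallest near p1 = 0.41, where p2 = 0.592 and p̄ = 0.501: n = (1.386 + 0.585)² / 0.1822² = 117, a total of 234. At p1 = 0.05 the total is 898. This is a separate matter, but it sets the scale for what follows.

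**The tests.** Let x1 and x2 be the quitters in each group, m = x1 + x2 and D = |x1(50 − x2) − x2(50 − x1)|.
- Pearson: X² = 100·D² / [m(100 − m)·50·50]
- (N-1): X² × 99/100
- Yates: replace D by max(D − 50, 0) in the Pearson formula

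Each is compared with 3.841. All 51 × 51 outcomes were enumerated with their binomial probabilities, under equal rates for size and under OR 2.09 for power.

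| Quit rate (control) | Size: Yates | Size: (N-1) | Power: Yates | Power: (N-1) | Loss (points) |
|---|---|---|---|---|---|
| 5% | 0.7% | 4.3% | 6.1% | 14.1% | 8.0 |
| 10% | 1.8% | 4.8% | 15.5% | 23.3% | 7.8 |
| 15% | 2.4% | 4.7% | 23.6% | 31.0% | 7.4 |
| 20% | 2.8% | 4.9% | 29.1% | 36.6% | 7.5 |
| 30% | 3.1% | 5.0% | 35.4% | 43.3% | 7.9 |
| 40% | 3.2% | 5.2% | 39.1% | 47.1% | 8.0 |
| 50% | 3.5% | 5.7% | 36.7% | 44.7% | 8.0 |

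At 8% the loss is 20.3 − 11.8 = 8.5 points, the largest of the rates checked. At every rate checked, Yates had the same rejection probability as Fisher's exact test.

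**Against a test that strictly holds 5%.** An exact unconditional (Boschloo-type) test, with maximum size 4.9%, has power of 10.6%, 19.8%, 33.2%, 42.3% and 41.6% at control rates of 5%, 10%, 20%, 30% and 40%. Yates loses 4.5, 4.3, 4.1, 6.9 and 2.5 points against it.

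**One table.** For 5/50 against 13/50: D = |5·37 − 13·45| = 400 and the denominator is 18·82·2500 = 3,690,000. Pearson X² = 100·400²/3,690,000 = 4.336. The (N-1) value is 4.293 (p = 0.038). Yates gives 100·350²/3,690,000 = 3.320 (p = 0.068).

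**Two visits.** The family-wise error was taken from a bivariate normal model in which each visit is tested at its actual size. The correlation between visits is assumed to be 0.8 to 0.5.
- Yates at both visits: 2.9% to 3.4% at a 10% quit rate, 4.5% to 5.2% at 20%, 5.1% to 5.9% at 40%.
- Two tests at a true 5%: 7.8% to 9.1%.

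**The case against.** The strongest defence is that Yates' test is valid. Its size never exceeds 3.5% at this sample size, and statisticians differ on whether to guard the nominal level or sit close to it. This stands. A reader might infer that naming the test beside an alpha of 0.05 is an error-control fault. It is not, because a test that rejects less often than alpha still respects alpha.

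A reader might also infer that the uncorrected alternatives hold 5% everywhere, so that the correction buys nothing. The enumeration does not support that. The (N-1) test is at or about 5% for quit rates of 5% to 30% (highest value checked 5.03%, at 25%), but reaches 5.2% at 40% and 5.7% at 50%. The score test from a logistic model without covariates is Pearson's test, with size 5.5% at a 15% quit rate. Part of the apparent gain is this excess, which is why the loss is smaller against the exact unconditional test.

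It is equally tempting to charge the plan with a family-wise error of 7.8% to 9.1% for leaving the visit open. That range belongs to uncorrected tests. With Yates at both visits the figure is about 3% to 6%. The unnamed visit is also a detail that a condensed article may leave to the full protocol or analysis plan, so on its own it is not a defect.

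Finally, Yates' test is not the only planned analysis of abstinence, since generalised linear modelling is also named. Nor does changing the test rescue the trial's power. Both points are correct. They limit the importance of the change, but it remains worth making.

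**Conclusion.** This is a cheap improvement, not the correction of an error. The named test is valid but inefficient, with a true size of 0.7% to 3.5% where 5% was allowed. At OR 2.09 it loses 7.4 to 8.5 points of power against the (N-1) test over the control rates checked, and about 2.5 to 7 points (5% to 40%) against an exact unconditional test that holds 5%.

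The size and power figures are exact for 50 analysed per group. The power figures depend on a control quit rate that the article does not give. The two-visit figures rest on a normal approximation and an assumed correlation of 0.5 to 0.8.

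With either test, power at OR 2.09 stays below 50% at every control rate. The sample-size shortfall is the larger problem and must be dealt with separately.

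**What to change.** In Data analysis, replace Yates' test with the (N-1) chi-squared test. If strict control at 5% is wanted, use an exact unconditional (Boschloo-type) test instead. Report the risk difference with a Newcombe 95% confidence interval. In the same sentence, name one visit as the main comparison, for example week 26, with week 13 secondary.

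The cost is one sentence, with no new participants or data. With the (N-1) test, the price is a true size slightly above 5% at high quit rates (5.2% at 40%, 5.7% at 50%). With the exact unconditional test, the price is a smaller gain in power.
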